## 2.2 Rationale

Catheter occlusion is an important complication of CVAD use in children. It has serious consequences, and is related to bloodstream infection and intravascular thrombosis which in turn can cause significant morbidity and mortality.

There is some evidence that measurement of line resistance in CVADs might predict the future development of catheter occlusion, that early intervention could prevent this, and that serial measurement of line resistance might guide the use of these interventions.

Catheter resistance monitoring will be performed using the Alaris® Syringe Module (Carefusion inc., San Diego, USA). The technique for resistance measurement involves use of the device at clinically relevant flow-rates and is expected to cause minimal inconvenience for participants and caregivers.

Occlusion occurs when line resistance rises beyond a threshold at which no flow can be produced at maximum safe pressure. The study aims to show that CRM can identify a rise in resistance before the threshold is crossed and before catheter dysfunction is clinically apparent. However, the technique remains exploratory as the baseline variability and rapidity of rise in resistance is unknown. A number of different patterns might emerge.

Figure 5 shows a diagram of possible resistance patterns leading to an inevitable occlusion event. Line A shows high baseline variability with an unpredictable course to occlusion. Line B shows a steady rise in resistance over time with minimal baseline variability and predictable eventual occlusion. Line C shows a very rapid rise in resistance immediately preceding an unpredictable occlusion event. Lastly, Line D shows a slower exponential rise in resistance with a potentially predictable occlusion event.

If Line A or C is eventually found to be descriptive of most *in vivo* events, CRM is unlikely to be of assistance due to high baseline variability or insufficient prior warning. Alternatively, Line B or D might make CRM a realistic option for assessing the need for pre-emptive intervention to prevent catheter occlusion.

**Figure 5. Diagram of possible patterns of change in resistance over time preceding catheter occlusion.**

[figure not shown]

If the CRM technique is found to be feasible and predictive of future events, it will open the way for future research examining the use of pre-emptive intervention to prevent occlusion, dysfunction, thrombosis and infection. This could have a major impact on supportive care for children with cancer who require central venous access for survival. CRM is also a component of ETHEL, another St. Jude initiated study which aims to determine the impact of ethanol lock therapy on the outcome of CLABSI.

For this study, only children and adolescents expected to be present at St Jude for assessment at least weekly will be eligible. However, if the technique is shown to be successful in the St Jude population, other populations may also benefit. Children with intestinal insufficiency receiving long-term TPN are at extremely high risk of catheter associated complications. Catheter removal and replacement is extremely serious for these children as exhaustion of potential CVAD sites can lead to death or intestinal transplantation. [Kaufman, 2001]

### **3.0 RESEARCH PARTICIPANT ELIGIBILITY CRITERIA AND STUDY ENROLLMENT**

According to institutional and NIH policy, the study will accession research participants regardless of gender and ethnic background. Institutional experience confirms broad representation in this regard.

### **3.1 Inclusion Criteria**

- 3.1.1 Receiving treatment for any disease at SJRCH
- 3.1.2 Age  $\geq 5$  years to  $< 25$  years
- 3.1.3 Single or double lumen tunneled CVAD (ports will not be eligible)
- 3.1.4 Participant anticipates being present weekly at SJRCH for at least 12 weeks

### **3.2 Exclusion Criteria**

- 3.2.1 Plan to remove CVAD within 12 weeks
- 3.2.1 Expected survival less than 12 weeks
- 3.2.3 Past enrollment in the CaRMA study or past catheter resistance monitoring

Females who are capable of becoming pregnant, or are breastfeeding, and males who plan to father children will all be eligible for enrollment. No pregnancy test will be required.

### **3.3 Research Participant Recruitment and Screening**

Research participants will be recruited from outpatient clinics and inpatient wards at SJRCH only.

Each recruitment day, a study staff member will approach treating clinicians to ask which patients might be appropriate for enrollment, based on the described inclusion and exclusion criteria. After obtaining permission from clinicians, potential participants will be approached by study staff and invited to enroll in the study.

### **3.4 Enrollment on Study at St. Jude**

A member of the study team will confirm potential participant eligibility as defined in Section 3.1-3.2, and complete and sign the 'Participant Eligibility Checklist'. The study team will enter the eligibility checklist information into the Patient Protocol Manager (PPM) system. Eligibility will be reviewed, and a research participant-specific consent form and assent document (where applicable) will be generated. The complete signed consent/assent form(s) must be faxed to the CPDMO to complete the enrollment process.

A log of eligible patients who declined enrollment and reasons for non-enrollment will be maintained. Catheter resistance monitoring is a component of ETHEL, another St. Jude initiated study examining the impact of ethanol lock therapy on outcomes of CLABSI however, none of the first five study participants eligible to participate in the CRM component chose to do so. With respect to the current study, if none of the first six, or less than two of the first 12 potential participants approached agree to participate, the study will be paused to review and, if possible, address the reasons for non-enrollment.

The CPDMO is staffed 7:30 am-5:00 pm CST, Monday through Friday. A staff member is available by pager Saturday, Sunday, and holidays from 8:00 am to 5:00 pm.

## **4.0 DESIGN AND METHODS**

### **4.1 Design and Study Overview**

The trial will be a single-group prospective study of weekly catheter resistance monitoring for 12 weeks.

Participants will be enrolled at any point during treatment.

The study aims to recruit 35 evaluable participants. Based on estimates by representatives of each hospital team, approximately 80 patients per year would be eligible for enrollment (Bone marrow transplant, 40; Leukemia, 10; Neurooncology, 15; Solid tumor, 15).

During the study period, participants will be monitored for CVAD related complications, adherence to CRM visits and participant/caregiver satisfaction.

Participants who receive thrombolytic therapy to restore CVAD patency, or whose CVAD is removed and replaced with another eligible tunneled CVAD will remain on study. The next CRM reading will act as a new baseline for each lumen.

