**Secondary Hypotheses:**

That adherence to weekly CRM will be high in children and adolescents treated at SJRCH

That clinically apparent catheter occlusion or dysfunction is preceded by a measurable rise in catheter resistance which is outside the range of baseline variability

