**Planned Analyses for Secondary Aims:**

Attendance at weekly visits over the study period for each participant will be expressed as a proportion of planned visits.

The change in catheter resistance from baseline over time will be described for each participant. Change from baseline for measurements preceding catheter occlusion or dysfunction events will be compared with other measurements.

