## DEFINITIONS

**Central venous access device (CVAD):** An intravenous catheter that terminates at or close to the heart or in one of the great vessels which is used for infusion, withdrawal of blood, or hemodynamic monitoring

**Catheter resistance monitoring:** Serial measurement of resistance to flow in the lumen(s) of a CVAD with the aim of identifying an increase in resistance greater than normal variation.

**Total CVAD occlusion:** Inability to flush and aspirate any lumen of a CVAD which does not resolve with standard techniques. Standard techniques include: Checking that the CVAD is not clamped or kinked, flushing, changing position, raising arms or coughing.

**CVAD occlusion to aspiration:** Inability to aspirate but not flush any lumen of a CVAD which does not resolve with standard techniques as above.

**CVAD occlusion to flush:** Inability to flush but not aspirate any lumen of a CVAD which does not resolve with standard techniques as above.

**CVAD dysfunction:** Subjective increase in pressure required to flush or aspirate any lumen of a CVAD which does not resolve with standard techniques as above.

**Intravascular thrombosis:** Radiologically proven total or subtotal occlusion of a large vein in which a CVAD has been placed. Thrombosis will be categorized as symptomatic if any of the following are noted: extremity swelling, redness or pain, or if there is clinical evidence of pulmonary embolism.

**Central line associated bloodstream infection:** For the purposes of this study, CLABSI will be defined according to the National Healthcare Safety Network (NHSN) definition, modified to account for local practice. [Centers for Disease Control, 2010]

Laboratory confirmed BSI, not secondary to infection at another site, where a central line (intravascular catheter which terminates at or close to the heart, or in one of the great vessels) is present within 48 hours of infection onset

**Laboratory-Confirmed BSI:** A bloodstream infection which meets one of the following criteria:

Criterion 1: Patient has a recognized pathogen cultured from one or more blood cultures; And organism cultured from blood is not related to an infection at another site.

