### **Treatment of catheter occlusion**

Administration of a thrombolytic agent, such as tPA, commonly restores CVAD patency. However, at least 10% of episodes necessitate device removal [Journeycake, 2006], and catheter occlusion was responsible for 9.5% of unplanned catheter removals in a large pediatric oncology cohort. [Weiner, 1992]

One recent retrospective study of tPA use for treatment of catheter occlusion or dysfunction in a large children's hospital found that 21.3% of attempts were unsuccessful. [Peng, 2011] The study included patients with cancer (52.6%). There was a significant difference in failure rates between tunneled lines (19%) and ports (53.8%).

Catheter occlusion which is not amenable to thrombolytic treatment usually requires surgical management to replace the line.

Even for successful tPA use, the cost is significant. Each dose of tPA is currently \$88, and St. Jude currently uses approximately 700 doses per year (\$61,000).

Although tPA use is generally safe, and major bleeding occurs in less than 0.03% of treatment episodes, there are other potential drawbacks of attempted catheter salvage. [Baskin, 2009] In a study of children receiving antibody treatment for neuroblastoma, one of three patients who had complete catheter occlusion developed catheter fracture with

migration of the distal fragment into the right atrium. [Kayton, 2008] This is a rare but life-threatening complication of catheter occlusion.

**Figure 2.** Catheter fracture during attempted salvage of occluded catheter. [Kayton, 2008]

[figure not shown]

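### After thrombolysis, Section 4.1 resets the baseline of every lumen of a retained catheter, so an existing rise in an untreated or incompletely cleared lumen is set to zero

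*Protocol*

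**What the plan says.** Section 4.1 states: "Participants who receive thrombolytic therapy to restore CVAD patency, or whose CVAD is removed and replaced with another eligible tunneled CVAD will remain on study". One rule then follows for both situations: "The next CRM reading will act as a new baseline for each lumen". It sets no condition that the thrombolytic worked and does not confine the reset to the lumen that was treated. Section 3.1 admits both single and double lumen tunneled catheters.

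The baseline enters the analysis through the Study Summary. For the secondary aim: "Change from baseline for measurements preceding catheter occlusion or dysfunction events will be compared with other measurements". The exploratory aims have a parallel comparison for thrombosis and bloodstream infection. The secondary hypothesis is: "That clinically apparent catheter occlusion or dysfunction is preceded by a measurable rise in catheter resistance which is outside the range of baseline variability".

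Three other places bear on the rule:

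- The Definitions treat occlusion as something that can affect a single lumen and can be partial. Occlusion to aspiration, for example, is "Inability to aspirate but not flush any lumen of a CVAD which does not resolve with standard techniques as above".
- Section 4.3 withholds resistance measurement only from lumens that are totally occluded, until they are open again.
- Section 2.1 cites a retrospective study of thrombolytic use that "found that 21.3% of attempts were unsuccessful" (19% for tunneled lines). It adds that occlusion not responding to thrombolysis usually ends in surgical replacement of the line.

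**The concern.** A replaced catheter is a new tube and needs a new baseline. After thrombolysis the tube is the same, and whether a new baseline is sensible depends on what happened to that particular lumen. The rule does not ask. Change from baseline at the reset visit is zero by definition, whatever the resistance then is.

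Two kinds of lumen are therefore misdescribed. One is the untreated lumen of a double lumen catheter, whose rise to date disappears because its neighbour was treated. The other is a treated lumen that is open enough to be measured but still narrowed, aspiration-occluded or dysfunctional, so that a raised reading becomes its reference. If such a lumen later has an event, the readings before it show a smaller change than the lumen has undergone since entry. The error runs toward not finding the rise that the study is looking for.

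**Working it through.** **1. The plan's own event figure.** Inputs: 35 evaluable participants (4.1), 2.0 to 2.2 events per 1000 catheter days (9.2.2), 15 weeks of outcome reporting (Study Summary).

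- 35 × 105 days × 2.0/1000 = 7.35
- 35 × 105 days × 2.2/1000 = 8.09

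This reproduces the stated expectation of about 8. Over the 12 weeks in which resistance is measured (84 days), the same formula gives 5.88 to 6.47.

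**2. Which lumens the reset can distort.**

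| Situation at the next reading | Effect of the reset |
|---|---|
| Catheter replaced | Appropriate |
| Treated lumen, cleared | Defensible |
| Treated lumen, still totally occluded | Not measured (4.3), so supplies no baseline until open |
| Treated lumen, retained, still partly obstructed, aspiration-occluded or dysfunctional | Existing rise set to zero |
| Untreated lumen of the same catheter | Any existing rise set to zero |

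**3. How much a reset can hide.** The paths below are assumptions. Only the starting value of 0.13 mmHg/ml/hr is taken from the protocol, as the in vitro mean for Catheter 1 in Section 2.1.

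- *Incompletely cleared lumen:* 0.13 at entry, 0.20 after treatment, 0.22 at the next visit. Against entry, 0.22/0.13 = 1.69, or +69%. Against the reset value, 0.22/0.20 = 1.10, or +10%, which lies inside the 20% maximum in vitro deviation from the mean that Section 2.1 reports.
- *Untreated lumen* rising each week by 10% of its entry value, reset at week 4. Readings at weeks 4 to 8 are +40, +50, +60, +70 and +80% against entry. After the reset (1.4/1.4, 1.5/1.4, 1.6/1.4, 1.7/1.4, 1.8/1.4) they are 0, +7, +14, +21 and +29%.
- *Noise for scale:* with the in vitro SD of 0.012, the difference of two readings has a 95% range of ±1.96 × √2 × 0.012 = ±0.033 mmHg/ml/hr. The untreated lumen's changes after reset are 0, 0.013, 0.026, 0.039 and 0.052, so the first three are within noise. Against entry they are 0.052 to 0.104, all outside it.

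**4. The opposite error.** Keeping the entry baseline in all cases has its own failure, because "Participants will be enrolled at any point during treatment" and the entry reading may already be raised. Assumed path: 0.20 at entry, cleared to 0.13, rising to 0.18. Against entry, 0.18/0.20 = 0.90, or −10%. Against the reset value, 0.18/0.13 = 1.38, or +38%. Here the reset is the better reference.

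**The case against.** **Failed treatment rarely leads to a distorted series.** A reader might multiply 8 expected events by the cited failure rates (8 × 0.19 = 1.5; 8 × 0.213 = 1.7) and infer that one or two events would restart from an obstructed baseline. The protocol does not support that. The product counts failed treatments and assumes that all 8 events receive a thrombolytic, whereas Section 4.5 also counts events that lead only to modified use or removal. Failed clearance usually ends in replacement, where the reset is correct, and a totally occluded lumen gives no reading. Distortion also needs a later event in the retained catheter with readings in between; the first event in each catheter is untouched. The share of double lumen catheters is not given either. This objection stands: no count can be given.

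**The original baseline is not always right.** A reader might infer that the reset should apply only to replaced catheters. Step 4 of the working shows why not, and by the cited rates most attempts succeed. This stands for treated, cleared lumens. It does not justify resetting untreated or uncleared ones.

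**The analysis is not confined to change from baseline.** That wording is in the Study Summary. Sections 4.4, 4.5, 9.2.2 and 9.3.3 speak of resistance results and graphs, with logistic models optional, and the pressure readings behind each resistance value are kept on the case report form. So it would be too strong to say that every analysis depends on the reset or that information is lost. The Study Summary comparison still uses a baseline, and Section 4.1 fixes which one.

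**Conclusion.** The point holds in limited form. As written, Section 4.1 resets all lumens of a retained catheter after patency-restoring thrombolysis, regardless of outcome and of which lumen was treated. For an untreated lumen, or a treated lumen measured while still impaired, this sets an existing rise to zero and biases the change-from-baseline comparison toward missing a rise before a later event.

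The effect on one affected series can be large (+69% becoming +10% in the assumed example), but how many series are affected cannot be derived from the protocol. The effect is confined to later events in retained catheters. It concerns the secondary occlusion and dysfunction aim and the exploratory thrombosis and bloodstream infection aims. The primary feasibility proportion does not use a baseline and is unaffected. The conclusion rests on reading the rule literally; the illustrations rest on assumed resistance paths and on in vitro variability, since Section 2.2 says that baseline variability in use is unknown. The change is worth making because events will be few and the remedy is cheap.

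**What to change.** In Section 4.1, apply the reset lumen by lumen:

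- all lumens of a replaced catheter take a new baseline;
- in a retained catheter, only a treated lumen whose recorded function was restored takes a new baseline (flushing and aspiration are already recorded at each visit under 4.3);
- untreated or uncleared lumens keep their existing baseline.

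For every lumen of a retained catheter after thrombolysis, flag later readings. Also report change from the original baseline (the first reading in that catheter) and absolute resistance by the catheter type recorded under Section 4.2, so that no conclusion depends on one choice of reference.

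The cost is one or two sentences, a few derived variables and slightly more to report, with no new measurement. The rule needs the treated lumen to be identified. Section 4.5 collects thrombolytic use without saying that the lumen is noted, so the case report form should be checked for that item.

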### **4.2 Baseline data collection**

Age, gender, primary disease type, remission status, treatment protocol and treatment week will be recorded at enrollment.

Catheter type, anatomic location, insertion date and current function will be recorded for the current catheter. Number of previous catheters within 12 months prior to enrollment and reasons for their removal will be recorded. Episodes of CLABSI, line occlusion or intravascular

thrombosis, and use of thrombolytic agents within 6 months prior to enrollment will be recorded.

### **4.3 Measurement of Catheter-Resistance**

Catheter-resistance in each lumen of the CVAD will be measured weekly by study staff with competencies in line care. This will occur in the medicine room or inpatient floor at St. Jude.

1. The CVAD will be accessed according to usual institutional practice. This will occur immediately after collection of laboratory tests where possible to standardize the procedure. No clamp/needleless connector will be used.
2. Subjective catheter function will be assessed by flushing and aspirating the CVAD and recorded on a case report form.
3. Normal saline will be administered at a predetermined constant flow-rate by the Alaris® Syringe Module (Carefusion inc., San Diego, USA). The pressure sensor will be placed at the estimated height of the right atrium (5cm below the sternal angle).
4. Pressure will be measured using the Alaris® Syringe Module (Carefusion inc., San Diego, USA) and will be recorded on a case report form.
5. The process will be repeated twice at 4 different flow-rates (usually 10ml/h, 50ml/h, 100ml/h, 150ml/h) for each lumen. Only flow-rates within the normal range for the population will be used. Figure 6 shows expected results for this procedure.
6. The line will be flushed and locked according to usual institutional practice.

If total occlusion of one or both lumens is identified at step 2, CRM will not be performed on involved lumens until patency is achieved.

It is anticipated that the CRM procedure will take 10-20 minutes per lumen to complete.

At each weekly visit, participants will be offered a \$5 gift card or other item of similar value.

### **4.4 Results of Catheter Resistance Monitoring**

CRM results will be considered usable if pressure readings are recorded for at least 3 different flow-rates for each lumen of the CVAD.

Results of catheter resistance measurement will not be communicated to the participant or treating team because interpretation is currently unclear and this is not a routine part of standard care.

The serial measurements of catheter resistance will be used to describe baseline variability for all participants. CRM results preceding catheter-related complications will be compared with all other results.

**Figure 6. Chart of expected results of measurement of line pressure at different flow-rates to determine resistance**

[figure not shown]

## 4.5 Outcome Assessment

### Primary Objective

Feasibility of CRM will be determined by describing the proportion of attended CRM visits for each patient which produce usable resistance data (i.e. any pressure reading for at least 3 predetermined flow rates for each lumen of the CVAD). Feasibility will only be measured at attended visits to allow discrimination between feasibility and adherence which is assessed separately.

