**Criteria for Evaluation:**

The primary outcome measure will be the proportion of attended CRM visits for each participant for which usable catheter resistance measurements are obtained for each lumen of the CVAD.

Catheter resistance will be measured by determining the gradient of a pressure-flow curve over a range of clinically relevant flow-rates. These data will be collected weekly for each lumen of the CVAD by the PI or trained study staff.

Other outcome measures include: changes in resistance preceding clinical events, attendance at planned weekly CRM visits and patient/caregiver satisfaction scores.

**Study Design:** The design will be prospective single-group feasibility study

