**Figure 4. Reproducibility of *in vitro* Catheter Resistance Monitoring**

[figure not shown]

For Catheter 1, mean resistance was 0.13 mmHg/ml/hr (Range 0.12 – 0.15; standard deviation 0.012) over 6 trials. For Catheter 2, mean resistance was 0.15 (Range 0.12 – 0.18; standard deviation 0.012) over 9 trials. Variability was small (maximum change from mean 20%).

By measuring pressure at multiple flow-rates in an *in vitro* system with the catheter tip set at various heights relative to the pump we were able model the effect of repeated measurement and difference in CVP or bed height, and demonstrated that these had minimal effect on measured resistance. These data show that *in vitro*, resistance measurement is feasible and reproducible.

Serial monitoring of catheter-resistance in patients without clinical evidence of catheter occlusion could demonstrate that occlusion events or other CVAD-related complications are predictable, and suggest an ideal time-point or other marker to guide intervention.

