## **9.0 STATISTICAL CONSIDERATIONS**

### **9.1 Analysis of Primary Objective**

To describe the feasibility of CRM in children and adolescents treated at St. Jude

The proportion of attended CRM visits which produce usable resistance data for all lumens of the CVAD will be recorded for each participant, and summary statistics, including median, range and standard deviation will be reported for the study population.

Estimated completion date: 11/01/2013

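### The usability rule behind the primary outcome tests only whether pressures were recorded, and it fails a visit when the protocol itself bars measuring an occluded lumen

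*Protocol*

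**What the plan says.** The Study Summary (Criteria for Evaluation) sets the primary outcome as the "proportion of attended CRM visits for each participant for which usable catheter resistance measurements are obtained for each lumen of the CVAD". Section 9.1 repeats the all-lumen condition: "The proportion of attended CRM visits which produce usable resistance data for all lumens of the CVAD will be recorded for each participant". It lists the median, range and standard deviation as summaries.

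Usability is fixed in two places. Section 4.4: "CRM results will be considered usable if pressure readings are recorded for at least 3 different flow-rates for each lumen of the CVAD". Section 4.5, under the primary objective: "any pressure reading for at least 3 predetermined flow rates for each lumen of the CVAD". Section 4.5 also restricts the denominator to attended visits, so that feasibility is kept apart from adherence.

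Three other statements bear on this:

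- Section 2.1 defines resistance as the gradient of the pressure-flow curve.
- Section 4.3, step 5, prescribes the measurement: "The process will be repeated twice at 4 different flow-rates", usually 10, 50, 100 and 150 ml/h.
- Section 4.3 also says that, for a total occlusion found at step 2, "CRM will not be performed on involved lumens until patency is achieved".

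**The concern.** The sole primary outcome is meant to show whether a resistance can be obtained at a visit. The rule asks for less than that. It does require different, predetermined rates in every lumen, so some completeness is tested. It does not ask that pressure rise with flow, that the second run be done, or that the two runs be compared. A flat or falling curve is scored as a success.

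The rule also errs in the other direction. A totally occluded lumen may not be measured, every lumen is needed, and the denominator is all attended visits. No section removes or separately classifies such a visit, so as written it is not usable, even if the other lumen was measured perfectly. Catheter occlusion is part of the secondary endpoint. The protocol takes care to separate feasibility from adherence, and caps planned visits for death, transfer and catheter removal in the adherence analysis. It takes no similar care to separate feasibility from the state of the catheter.

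**Working it through.** **Precision of a minimally usable visit**

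Inputs: the four usual rates and the repeat from section 4.3, read as two runs and so eight readings per lumen. Assumption: equal, independent error in each pressure reading. The least-squares slope then has a standard error proportional to 1/√Sxx, where Sxx is the sum of squared deviations of the flow-rates from their mean.

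Full procedure: the mean rate is 77.5, so Sxx for one run = 67.5² + 27.5² + 22.5² + 72.5² = 11,075. Two runs give 22,150. The standard error ratio is √(22,150/Sxx).

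| Three rates (ml/h) | Sxx, single | SE ratio, single | Sxx, duplicate | SE ratio, duplicate |
|---|---|---|---|---|
| 10, 50, 100 | 4,066.7 | 2.33 | 8,133.3 | 1.65 |
| 50, 100, 150 | 5,000 | 2.10 | 10,000 | 1.49 |
| 10, 100, 150 | 10,066.7 | 1.48 | 20,133.3 | 1.05 |
| 10, 50, 150 | 10,400 | 1.46 | 20,800 | 1.03 |

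Single readings at three rates therefore give a slope standard error 1.46 to 2.33 times that of the full procedure. Residual degrees of freedom fall from 8 − 2 = 6 to 3 − 2 = 1, so the fit can barely be checked. Requiring both runs brings the ratio down to 1.03 to 1.65.

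**Size of the occluded-lumen effect**

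The plan's own figure comes first. Section 9.2.2 expects about 8 episodes from a rate of 2.0 to 2.2 per 1000 catheter days. With 35 participants and the 15-week (105-day) reporting period:

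- 35 × 105 × 2.2/1000 = 8.09
- 35 × 105 × 2.0/1000 = 7.35

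The stated figure reproduces at the upper rate. Measurements run only for 12 weeks (84 days):

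- 35 × 84 × 2.0/1000 = 5.88
- 35 × 84 × 2.2/1000 = 6.47

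I therefore use 6 to 8 events over 35 × 12 = 420 planned visits, all taken as attended. The protocol gives neither the share of events that are total occlusions still present at a visit nor how many visits each affects. Both are assumed:

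- Low: 25% of 6 events, one visit each: 1.5/420 = 0.4 points.
- High: 100% of 8 events, one visit each: 8/420 = 1.9 points.
- Extreme: 100% of 8 events, three visits each: 24/420 = 5.7 points.

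For one child with 12 attended visits, one affected visit gives 11/12 = 91.7%, a loss of 8.3 points. For a child with 4 attended visits it gives 3/4 = 75%.

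**The case against.** The strongest reply is that feasibility and reproducibility are separated on purpose. The primary aim is descriptive and has no success threshold. Section 4.4 plans to describe baseline variability from the serial measurements, and section 2.2 says that high variability would make monitoring unlikely to help. A technique with unstable results would therefore show up elsewhere. This stands in part: poor reproducibility would not stay hidden. It does not rescue the primary label, because the outcome claims usable resistance data and the rule does not ask whether the readings give a credible gradient.

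Second, the ratios compare the bare permitted minimum with a complete visit, and nothing suggests that minimum visits would be common. That is right. The figures show what the rule cannot tell apart, not how often it happens.

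Third, failure to measure an occluded lumen may fairly count as a practical limit of the method. Either convention is defensible if stated, but neither is stated. The bar covers only total occlusion still present at step 2. It does not cover aspiration-only or flush-only occlusion, or dysfunction.

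Some stronger readings are tempting but unsupported:

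- A reader might infer that the primary outcome would sit near 100% whatever the technique's quality. No figure in the protocol shows this.
- A reader might picture a child whose lumen is lost after visit 3, scoring 3/12 = 25% and moving a 35-child mean by 0.75/35 = 2.1 points. This is only an illustration. Section 4.5 lists long-term modification of catheter use as a criterion for counting an event and does not forecast it. Section 2.1 says that thrombolysis commonly restores patency, and section 6.1 ends monitoring at permanent removal. Section 9.1 lists the median and not the mean, and one child barely moves a median of 35.
- A reader might take the 20% in vitro maximum deviation as a ready agreement limit. It describes single trials against the mean of 6 or 9 bench trials, not two slopes at one visit in a patient.

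**Conclusion.** The concern holds as a badly fixed definition of the sole primary outcome. It is not a detail left to a later plan, because sections 4.4 and 4.5 state the rule outright.

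The missing quality condition is the weightier half, since it can affect any visit. The 1.46 to 2.33 ratio rests on equal, independent reading error and on the usual four rates. The occluded-lumen half is an inference from sections 4.3, 4.5 and 9.1 read together, as no sentence states it. Its pooled effect is small, about 0.4 to 1.9 points at one visit per event with the share of total occlusions assumed, although it can matter for one child.

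The documents do not support the conclusion that the outcome cannot separate feasible from infeasible monitoring. They support the narrower one: it credits some visits without a credible slope, and debits some for the state of the catheter and not the performance of the method.

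**What to change.** In sections 4.4 and 4.5, with 9.1 and the Study Summary brought into line:

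1. Define a lumen-visit as usable only if both runs give readings at three or more predetermined rates and the fitted slope is positive.
2. Report the any-reading proportion, as now defined, as a secondary result.
3. Report the within-visit difference between the two run slopes descriptively. Set no 20% pass/fail limit, because section 2.2 says that baseline variability is unknown.
4. Take the primary proportion over lumens eligible for measurement at attended visits. Tabulate lumens totally occluded at step 2 separately as not measured because occluded.
5. Give the all-lumen, all-attended-visit proportion as a sensitivity result.

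The duplicate readings and the step 2 function check are already planned, so no visit, procedure or clinical rule changes. The cost is a little more analysis and a possibly less favourable headline proportion. A positive slope is a minimum and does not show that a measurement is good, which is why the within-visit difference should be reported beside it.
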